## Abstract

**Background:**

Type 2 diabetes (T2DM) is a major risk factor for myocardial infarction. Thrombus aspiration was considered a good way to deal with coronary thrombus in the treatment of acute myocardial infarction. However, recent studies have found that routine thrombus aspiration is not beneficial. This study is designed to investigate whether intracoronary artery retrograde thrombolysis (ICART) is more effective than thrombus aspiration or percutaneous transluminal coronary angioplasty (PTCA) in improving myocardial perfusion in patients with ST-segment elevation myocardial infarction (STEMI) undergoing primary percutaneous coronary intervention (PPCI).

**Methods/Design:**

IntraCoronary Artery Retrograde Thrombolysis (ICART) vs. thrombus aspiration or PTCA in STEMI trial is a single-center, prospective, randomized open-label trial with blinded evaluation of endpoints. A total of 286 patients with STEMI undergoing PPCI are randomly assigned to two groups: ICART and thrombus aspiration or PTCA. The primary endpoint is the incidence of >70% ST-segment elevation resolution. Secondary outcomes include distal embolization, myocardial blush grade, thrombolysis in myocardial infarction (TIMI) flow grade, and in-hospital bleeding.

**Discussion:**

The ICART trial is the first randomized clinical trial (RCT) to date to verify the effect of ICART vs. thrombus aspiration or PTCA on myocardial perfusion in patients with STEMI undergoing PPCI.

**Clinical Trial Registration:**

[https://www.chictr.org.cn/], identifier [ChiCTR1900023849].

## Background

Patients with type 2 diabetes (T2DM) are at high risk and have a poor prognosis of myocardial infarction, especially after ST-segment elevation myocardial infarction (STEMI). STEMI is due to plaque rupture leading to intracoronary thrombosis, thus blocking the coronary artery (1, 2). The strategy to treat myocardial infarction is to open the infarct-related coronary artery to achieve reperfusion as soon as possible (3). However, in the process of opening the occluded vessels, it leads to myocardial damage. This phenomenon is called reperfusion injury (4). Myocardial death caused by reperfusion accounts for 25% of the total death area. Animal experiments show that the proportion is even as high as 50% (5). Reperfusion injury can cause reperfusion arrhythmia, myocardial stunning, microvascular occlusion, intramyocardial hemorrhage, and lethal myocardial reperfusion injury (6).

At present, methods of opening occluded vessels include intravenous thrombolysis, primary percutaneous coronary intervention (PPCI), and emergency coronary artery bypass grafting (CABG) (7, 8). The advantage of intravenous thrombolysis is that it can be implemented in general hospitals and even primary hospitals, and can be carried out quickly before hospitalization or even in ambulances (9–11). However, the success rate of intravenous thrombolysis is relatively low (12, 13). Even after intravenous thrombolysis success, emergency percutaneous coronary intervention (PCI) should be performed within 24 h, which increases the risk of hemorrhagic events or even fatal hemorrhage. Therefore, intravenous thrombolysis was gradually reduced or even stopped in the hospitals that could perform primary PCI in time or quickly transfer to primary PCI hospitals (7). Because of the complexity of CABG and the high requirement of patients’ own conditions, it is relatively difficult to carry out emergency CABG (8).

Primary percutaneous coronary intervention is still the best way to treat acute myocardial infarction because of its simple operation and exact effect (14). Thrombus load is an independent risk factor for PPCI. Slow-flow and no-reflow after stent implantation affect the prognosis (15). There are two ways to deal with thrombus before PPCI. The first is thrombus aspiration (16). However, routine thrombus aspiration before PPCI does not reduce the rate of all-cause mortality, rehospitalization of myocardial infarction, or stent thrombosis, and even increase the risk of stroke (17). Even in patients with high thrombus burden, routine thrombus aspiration does not improve outcomes (18). The second is to give antithrombotic or thrombolytic agents through the transcatheter, such as glycoprotein (GP) IIb/IIIa inhibitors, alteplase, et al. (19). However, due to the blood flow erosion, antithrombotic agents, and thrombolytic agents cannot stay for a long time at the thrombus site, affecting the drug effect; if the dosage is increased, the hemorrhagic risk will increase at the same time (20). It has also been studied that thrombolytic drugs are given after thrombus aspiration (21), the efficacy is similarly affected for the above reasons. There is still a long way to go to solve the problem of intracoronary thrombus, especially in patients with large thrombus burdens.

The sequence of continuous thrombosis is white thrombus, mixed thrombus, and red thrombus. The white thrombus in the head is mainly composed of platelets. The red thrombus at the tail end is mainly composed of red cells within the fibrin network (22). According to the characteristics of thrombus, we put forward the method of ICART, applied it to a small sample population, and achieved a certain effect (23). Only 10% of intravenous thrombolysis is needed for the ICART procedure. Before the newly formed thrombus is destroyed, a very high concentration of thrombolytic agent is produced in the red thrombus of the occluded vessel, which could stay for a long time, resulting in a very high thrombolytic efficiency, and reducing the incidence of no-reflow and slow-flow. At the same time, due to the slow opening of occluded vessels, there is a reperfusion preadaptation, which can reduce the reperfusion injury in theory. At the same time, low-dose thrombolysis does not increase the risk of hemorrhage and stroke. ICART may provide a new plan to solve thrombus burden in STEMI. However, there were only eight cases in the previous study (23). Therefore, we intend to verify the effect of ICART vs. thrombus aspiration or PTCA on myocardial perfusion in patients with STEMI undergoing PPCI.

## Study Design

The ICART trial is a single-center, prospective, randomized controlled trial with a blinded evaluation of endpoints (Figure 1). A total of 286 patients with STEMI undergoing PPCI were randomly divided into ICART or thrombus aspiration or PTCA groups. Randomization is performed by the Empower network random system when deciding to perform PCI. The study was approved by the institutional committee on human research of the Chinese People’s Liberation Army General Hospital and complies with the declaration of Helsinki. The protocol of this trial has been registered at chictr.org.cn (ChiCTR1900023849).

**FIGURE 1 F1:**
[figure not shown]
The ICART trial flow chart. ICART, intracoronary artery retrograde thrombolysis; STEMI, ST-segment elevation myocardial infarction; PCI, percutaneous coronary intervention; PTCA, percutaneous transluminal coronary angioplasty.

## Study Population

All consecutive STEMI patients who are ready to receive primary PCI are suitable for inclusion. The inclusion criterion includes: (1) STEMI with chest pain lasting 30 min to 12 h; (2) older than 18 years old; (3) volunteered and signed informed consent. The exclusion criteria includes: (1) active peptic ulcer; (2) severe hepatic or renal insufficiency; (3) pregnancy; (4) uncontrolled hypertension; (5) rescue PCI after thrombolytic therapy; (6) unable to sign informed consent; (7) less than 18 years old; (8) left main coronary artery disease; (9) cardiogenic shock; (10) mechanical complications after myocardial infarction (e.g., interventricular septum perforation, papillary muscle rupture); (11) recent history of major surgery, trauma, hemorrhagic disease, cerebrovascular accident, or thrombocytopenia; (12) previous history of CABG; (13) other obvious abnormal signs, laboratory tests, and clinical diseases. According to the judgment of the clinician, the patients are not suitable for the study.

## Preparation of Visualized Thrombolytic Agents and Process of Intracoronary Artery Retrograde Thrombolysis

As we previously described (23), visualized thrombolytic agents are made by dissolving 100,000 units urokinase or 5 mg prourokinase with 15 ml physiological saline and 5 ml iopromide.

The flow diagram for the ICART system is shown in Figure 2. Coronary angiography identifies the occluded coronary artery. First, the guidewire is sent to the distal end of the culprit’s vessel. A microcatheter or a cut balloon is sent to the occluded section through the guidewire. One milliliter of thrombolytic cocktail is bolus-injected through the microcatheter, which is repeated every 30 s. The effect of thrombolysis is observed by X-ray.

**FIGURE 2 F2:**
[figure not shown]
Pattern diagram of intracoronary artery retrograde thrombolysis system. After the passing of the wire, a microcatheter or a cut balloon is sent to the occluded section through the guidewire. One milliliter of thrombolytic cocktail is bolus-injected through the microcatheter to the distal lumen of the vessel, which is repeated every 30 s.

## Treatment

Before PCI, ICART or thrombus aspiration is decided according to the grouping. Thrombus is aspirated by the Export aspiration catheter (Medtronic Inc., Santa Rosa, CA, United States) as previously described (24). Finally, a stent is implanted. In certain patients, pre- or postdilatation with a balloon may be necessary.

Patients are given a loading dose of aspirin (300 mg) and ticagrelor (180 mg) or clopidogrel (600 mg), and are diagnosed STEMI by electrocardiography. It’s up to the operator to decide whether to use heparin or bevaludine for anticoagulation. In the setting of STEMI, radial access is preferred. In patients with radial artery pathways, sheaths are pulled out immediately following the PCI procedure. The femoral approach is reserved for patients without the radial approach. Sheaths are exchanged immediately at the end of the PCI procedure by the Angio-Seal device (St. Jude Medical, Inc., St. Paul, MN, United States). After PCI, tirofiban is used for 36 h. Then low molecular weight heparin is given for 1–3 days after tirofiban. According to the international guidelines, standard post PCI medication includes aspirin (100 mg), ticagrelor (90 mg bid), or clopidogrel (75 mg), beta-blockers, lipid-lowering drugs, and angiotensin converting enzyme inhibitors or angiotensin II receptor blockers (8).

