## Endpoints Assessment

The primary endpoint is to observe the probability of ST-segment resolution > 70% acquired before and 30–60 min after PPCI.

Secondary endpoints include:

1.Angiographic endpoints: TIMI flow grade, distal embolization, no reflow, slow flow, side branch occlusion, myocardial blush grade post-PPCI.2.Electrocardiographic end points: residual ST-segment deviation 30–60 min after primary PCI.3.Enzymatic infarct size.4.Mortality and Major Adverse Cardiac Events: All-cause death, cardiogenic death, cardiogenic shock, reinfarction, revascularization of target vessels, malignant arrhythmia, NYHA class IV heart failure, stent thrombosis, and myocardial infarction rehospitalization are to be registered at 30 days and 1 year.

Safety endpoints consist of in-hospital hemorrhagic and stroke complications.

Furthermore, the primary and secondary endpoints will be analyzed in a preset subgroup, which is defined as:

1.Age (<65 vs. >65 years)2.Gender3.Smoker4.Diabetes mellitus5.ST-segment resolution6.Number of diseased vessels (multi-vessel vs. single vessel)7.Proximal lesions8.Infarct-related artery [left anterior descending artery (LAD) vs. non-LAD]9.Bivalirudin10.Ischemic time (<3 vs. >3 h)11.Initial TIMI thrombus grade12.Angiographic presence of thrombus13.Intra-aortic artery balloon pump14.Left ventricular ejection fraction15.Type of P2Y12 inhibitor16.Killip class17.Symptom onset18.Pre-procedural TIMI flow19.Post-procedural TIMI flow20.Post-PCI myocardial blush grade21.Pacing use.

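### The operator may choose heparin or bivalirudin with the open-label arm already known, so an arm difference in bleeding may not be attributable to the lytic and the bivalirudin subgroup is not protected by randomisation

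*Protocol article*

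**What the plan says.** The Abstract describes a "single-center, prospective, randomized open-label trial with blinded evaluation of endpoints". On timing, Study Design states: "Randomization is performed by the Empower network random system when deciding to perform PCI". The Treatment section says that the allocated strategy is settled before PCI according to the group.

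The same section sets out the background antithrombotic treatment:

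- **Procedural anticoagulant:** "It’s up to the operator to decide whether to use heparin or bevaludine for anticoagulation" (the second drug is read here as bivalirudin, the name used in the subgroup list).
- **Antiplatelet loading:** "Patients are given a loading dose of aspirin (300 mg) and ticagrelor (180 mg) or clopidogrel (600 mg), and are diagnosed STEMI by electrocardiography". Who chooses between the two P2Y12 agents is not stated.
- **Antiplatelet maintenance:** "standard post PCI medication includes aspirin (100 mg), ticagrelor (90 mg bid), or clopidogrel (75 mg"). Again no decider is named.
- **Tirofiban:** "After PCI, tirofiban is used for 36 h". No choice and no arm difference is described.
- **Low molecular weight heparin:** "Then low molecular weight heparin is given for 1–3 days after tirofiban". Who sets the length within that range is not stated.

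Under Endpoints Assessment: "Safety endpoints consist of in-hospital hemorrhagic and stroke complications". The Abstract also lists in-hospital bleeding among the secondary outcomes. Endpoints Assessment then presets subgroups for the primary and secondary endpoints, two of which are bivalirudin and type of P2Y12 inhibitor.

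**The concern.** One arm receives an intracoronary thrombolytic and the other does not. The Background itself notes that larger doses of such agents carry more haemorrhagic risk. An operator who knows that a lytic is about to be given could reasonably let that influence the anticoagulant. Nothing in the article asks for the choice to be made before the arm is known, or independently of it.

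Two things are at stake.

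1. **Interpretation of bleeding.** The Background claims that low-dose thrombolysis adds no haemorrhage or stroke risk, and it cites only eight earlier ICART cases. This trial will be read as a test of that claim. If the background anticoagulant differs by arm, the bleeding contrast no longer isolates the lytic. Blinded assessment does not help, because the anticoagulant acts on bleeding itself and not only on how bleeding is judged. Adjusting for the drug actually used is not a clean repair either, because that drug may have been chosen in response to allocation.

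2. **The bivalirudin subgroup.** A subgroup defined by something decided after allocation can contain different kinds of patient in each arm. The treatment comparison inside it is then no longer a randomised one, and this applies to the primary endpoint as well.

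**Working it through.** **Sequence of events, from the article**

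1. PCI is decided and allocation is issued (Study Design).
2. The trial is open-label, so the operator who carries out the allocated strategy knows the arm (Abstract; Treatment).
3. The operator chooses heparin or bivalirudin (Treatment). No section places this before step 1.
4. In-hospital bleeding is counted (Endpoints Assessment).

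Step 3 can therefore follow step 2. For the P2Y12 agent the order is less clear. The loading sentence is tied to ECG diagnosis of STEMI, so the agent may already have been given before randomisation.

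**The plan's own figure**

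The article states no bleeding rate, so there is no bleeding figure to reproduce. The total of 286 concerns ST-segment resolution (56.6% vs 75%, two-sided 5%, 90% power, 5% loss). Common normal-approximation formulas at 1:1 give 284 to 292. That figure is not affected by this point.

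**Illustration on assumed values**

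Assume bleeding without the lytic of 6% on one anticoagulant (A) and 4% on the other (B). Nothing is implied about which drug is A or B. Let R be the true lytic risk ratio, and let s₁ and s₀ be the shares of ICART and control patients on B.

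- ICART risk = R × [(1 − s₁) × 6% + s₁ × 4%]
- Control risk = (1 − s₀) × 6% + s₀ × 4%

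With R = 1.5 the ICART risks by agent are 9% and 6%. For s₁ = 0.8 and s₀ = 0.2:

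- ICART: 0.2 × 9% + 0.8 × 6% = 6.6%
- Control: 0.8 × 6% + 0.2 × 4% = 5.6%
- Ratio: 6.6 / 5.6 = 1.18

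| Share on B, ICART / control | ICART risk (R = 1.5) | Control risk | Observed ratio, R = 1.5 | Observed ratio, R = 1 |
|---|---|---|---|---|
| 50 / 50 | 7.5% | 5.0% | 1.50 | 1.00 |
| 60 / 40 | 7.2% | 5.2% | 1.38 | 4.8 / 5.2 = 0.92 |
| 80 / 20 | 6.6% | 5.6% | 1.18 | 4.4 / 5.6 = 0.79 |
| 40 / 60 | 7.8% | 4.8% | 1.63 | 5.2 / 4.8 = 1.08 |
| 20 / 80 | 8.4% | 4.4% | 1.91 | 5.6 / 4.4 = 1.27 |

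A moderate imbalance leaves most of a true excess visible. A large one hides most of it. An imbalance in the other direction inflates the ratio, or produces an excess where the lytic has no effect.

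The pattern does not depend on one pair of rates. With a 70 / 30 split and R = 1.5, assumed rates of 8% and 5%, 10% and 6%, and 12% and 6% give observed ratios of 1.25, 1.23 and 1.15.

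**What the trial could detect anyway**

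At 143 per arm (1:1 assumed), 7.5% vs 5.0% means about 10.7 vs 7.2 expected events, and power is about 14%. The 80 / 20 case means about 9.4 vs 8.0 events.

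**The case against.** **A condensed article.** The article cites a full protocol (V1.0) that is not shown. Form fields, logs of switches and drug-use tables commonly sit there, so their absence here is no fault. That stands. The point rests on what the article does state: the anticoagulant is the operator's choice, the trial is open-label, and allocation comes when PCI is decided. An analysis plan could not undo a choice already made at the bedside.

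**The other drugs.** A reader might infer that the operator also picks the P2Y12 agent and the heparin length after seeing the arm. The article does not say so. It leaves both open without naming who decides, and P2Y12 loading may precede randomisation. They are open choices that could vary by arm, and no more than that.

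**Motive.** The article does not say that either anticoagulant bleeds less, or that operators will choose by arm. An operator who accepts the Background's claim of no added bleeding has less reason to do so. This stands: an imbalance is possible but not shown.

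**Low power.** With about 14% power for a 1.5-fold excess on the assumed rates, the bleeding comparison would be inconclusive even with identical background treatment. This also stands, and the change would not make it conclusive. It would still remove a source of bias in the estimate.

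**Visibility.** Presetting bivalirudin and P2Y12 subgroups implies that use is recorded, so an imbalance could be seen. Seeing it does not prevent it, and the subgroup split inherits the problem.

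**Conclusion.** The point holds for the procedural anticoagulant. It can be chosen with the arm known, and if use then differs by arm, a bleeding difference cannot be cleanly attributed to the lytic. The randomised comparison of the two strategies, each with whatever background treatment it attracts, remains valid. It would go too far to call the bleeding comparison invalid or to say that the arms will differ. The bivalirudin subgroup is defined by a choice that can follow allocation, so the comparison within it lacks the protection of randomisation.

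The size depends wholly on assumed rates and splits. A true ratio of 1.5 appears as 1.38 under a modest split and 1.18 under a strong one, and as 1.63 and 1.91 if the splits run the other way. The overall primary comparison and the sample size are not shown to be affected. This is a modest weakness that is almost free to correct.

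**What to change.** - Add to the existing Empower randomisation form, completed before the allocation is displayed, the intended procedural anticoagulant and the P2Y12 agent chosen or already given.
- Record the reason for any later switch.
- Define the bivalirudin and P2Y12 subgroups by that entry, not by the drug eventually used.
- Report actual antithrombotic use by arm, including the length of low molecular weight heparin, beside the bleeding results.
- In the report, describe the bleeding contrast as one between strategies, and attribute a difference to the lytic only as far as background use is similar by arm.

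The choice of drug and duration stays with the treating team, and no clinical rule is proposed. The cost is two form fields, a sentence in the protocol, a table in the report and a few seconds before randomisation.

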### Electrocardiography

A standard 18-lead ECG is acquired at first medical contact. A standard 12 lead ECG is performed 30–60 min after PPCI. Times of symptom manifestation, arrival at the hospital, guidewire passing, thrombolysis, balloon dilatation, end of PCI, and ECG are recorded. The magnitude of ST-segment deviation is calculated 60 ms from the J-point. The ST segment of post-intervention ECG at 30–60 min is compared with that of the ECG at presentation. ST-segment elevation resolution is defined as complete (>70%), partial (30–70%), or absent (<30%) (Trials 2009, 10:90). Residual ST-segment deviation after PCI is counted as the sum of residual ST-segment depression and elevation in all leads (25). All ECG data are analyzed by a physician who is blinded to the clinical grouping and data.

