## Infarct Size

The infarct size is estimated by serial monitoring of cardiac markers such as creatine kinase (CK), creatine kinase-MB (CK-MB), and troponin T. Blood samples are taken at baseline and 3, 6, 9, 12, 18, 24, and 48 h after PCI. Peak value, time to peak release as well as area under the curve are determined.

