## Statistical Considerations

### Sample Size Estimation

It has been reported that the incidence of ST-segment elevation resolution >70% has been reported to be 56.6% in STEMI patients treated with thrombus aspiration (24). We hypothesize that ICART administration during PCI increases the incidence of ST-segment elevation resolution >70–75%. To detect this difference between ICART and thrombus aspiration or PTCA groups, 286 patients are required to reach a 5% significance level (two-sided) with 90% power, which allows 5% of cases to fall off.

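### Residual ST-segment deviation is a continuous post-PCI sum, but the only model stated for it is logistic regression, with no presentation term named

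*Protocol article*

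**What the plan says.** The Endpoints Assessment section lists the electrocardiographic secondary endpoint as "residual ST-segment deviation 30–60 min after primary PCI". The Electrocardiography section defines it: "Residual ST-segment deviation after PCI is counted as the sum of residual ST-segment depression and elevation in all leads". Both describe a quantity read from the post-procedure ECG only.

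The Electrocardiography section also provides for an 18-lead ECG at first medical contact and a 12-lead ECG 30–60 min after the procedure. ST deviation is read 60 ms after the J-point, and the later ECG is compared with the presentation ECG to classify ST resolution. That comparison supports the primary endpoint, resolution above 70%. It is not carried over to residual deviation.

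Under Statistical Analysis, a single sentence assigns multiple logistic regression to the primary and secondary endpoints without naming covariates. The next sentence says that means and standard deviations will be reported.

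**The concern.** Two faults meet in this endpoint. First, a sum of ST deviation over leads is continuous. Binary logistic regression needs a two-level outcome, and the article gives no cut-point for this sum. As written, the endpoint has no workable model; the only stated summary that fits it is the mean and SD.

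Second, no presentation term is named. If presentation and post-procedure ST deviation are correlated, a model without the presentation value leaves explainable variation in the error term. The ECG that would supply this value is already taken in every patient because the primary endpoint needs it.

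At stake is the precision of the only quantitative ECG endpoint listed, and the freedom to choose a model and covariates after the data are seen.

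**Working it through.** **1. The plan's own figure.** Sample Size Estimation takes a control rate of "56.6% in STEMI patients treated with thrombus aspiration" and expects that ICART "increases the incidence of ST-segment elevation resolution >70–75"%, read here as a rise to 75% of patients with resolution above 70%. It states that "286 patients are required to reach a 5% significance level (two-sided) with 90% power", "which allows 5% of cases to fall off". The allocation ratio is not stated ("randomly assigned to two groups: ICART and thrombus aspiration or PTCA"); 1:1 is assumed. With unpooled variance:

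n per arm = (1.960 + 1.282)² × (0.566 × 0.434 + 0.75 × 0.25) / (0.75 − 0.566)² = 10.507 × 0.4331 / 0.03386 = 134.4, rounded up to 135.

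135 / 0.95 = 142.1, rounded up to 143 per arm, or 286 in total. The stated figure is reproduced. (Pooled variance gives 138 per arm, or 292 after the same inflation.) This calculation concerns the primary endpoint only, so nothing below alters it.

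**2. Setting for residual deviation.** Take 135 evaluable patients per arm and work in SD units of the post-procedure sum.

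- Standard error without baseline: √(2/135) = 0.122 SD.
- Difference detectable with 80% power without baseline: (1.960 + 0.842) × 0.1217 = 0.341 SD. This is a reference effect for comparing methods; it is not in the documents.
- The correlation r between presentation and post-procedure sums is not in the documents. It is assumed over the range 0.2 to 0.7.

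**3. Formulas.**

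- Residual variance: 1 for the post-procedure value alone; 1 − r² when adjusted for presentation; 2(1 − r) for an unadjusted change score, assuming equal SDs.
- Gain in effective sample size from adjustment: 1/(1 − r²) − 1.
- Power: Φ(0.341 / (0.1217 × √variance) − 1.960).

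| r | 1 − r² | SE ratio √(1 − r²) | 270 patients are worth | Gain | Power, adjusted | Power, change score |
|---|---|---|---|---|---|---|
| 0.2 | 0.96 | 0.98 | 281 | 4% | 81.6% | 60.1% |
| 0.3 | 0.91 | 0.95 | 297 | 10% | 83.6% | 65.8% |
| 0.5 | 0.75 | 0.87 | 360 | 33% | 89.9% | 80.0% |
| 0.7 | 0.51 | 0.71 | 529 | 96% | 97.5% | 95.1% |

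The reference in each row is 80% power for the post-procedure value alone. An unadjusted change score loses to that value below r = 0.5, equals it at 0.5 and beats it above. The adjusted model is better than both in every row.

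**4. Chance imbalance.** A baseline difference between arms of one standard error (0.122 SD) shifts the unadjusted estimate by r × 0.122 SD: 0.024, 0.037, 0.061 and 0.085 SD at r = 0.2, 0.3, 0.5 and 0.7. Averaged over randomisations the shift is zero, and the unadjusted standard error already allows for it.

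**5. Availability of the covariate.** The presentation ECG has 18 leads and the later one 12, while the definition sums over all leads. The two sums match only if the presentation sum is restricted to the 12 leads common to both. The article describes no summed presentation deviation, so it would have to be derived.

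**The case against.** The strongest reply is that the two ECG passages define an endpoint and do not say how the arms are compared. The one statement on comparison names a multivariable model, and its covariates may well be listed in an analysis plan or full protocol that is not shown. A reader might infer that residual deviation will be compared unadjusted. The article does not say so, and silence on covariates in a condensed article is not an error. That part of the reply stands.

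It does not rescue the stated model. Whatever its covariates, logistic regression does not take a continuous sum as its outcome unless the sum is cut, and no cut is given. The t-test and Mann-Whitney test in the same section follow the sentence on baseline characteristics. If they were meant for continuous endpoints as well, they would still carry no baseline term.

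Other stronger readings also fail:

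- **Bias.** A reader might infer that omitting the presentation value biases the result. Under randomisation, chance imbalance costs precision; it is not systematic bias, and the unadjusted test keeps its type I error.
- **Same quantity at presentation.** The differing numbers of leads show that an identical sum is not recorded.
- **Enzymes.** The Infarct Size section says "Blood samples are taken at baseline and 3, 6, 9, 12, 18, 24, and 48 h after PCI". A reader might infer that the baseline enzyme value goes unused. The article does not say how that sample enters the analysis, and it may itself be a point on the area under the curve.
- **A faulty definition.** Residual deviation is by its nature what remains after the procedure. The definition can stay as the outcome; what needs changing is the model.

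Finally, the primary endpoint already uses the presentation ECG through percent resolution. That is true, but it is dichotomised at 70% and does not replace an analysis of the quantitative endpoint.

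**Conclusion.** The point holds as a badly fixed analysis for one secondary endpoint: the stated model does not suit a continuous sum, and no presentation term is named although the presentation ECG is taken in every patient. Adjustment would add about 4% to 10% to the effective sample size if the correlation is 0.2 to 0.3, 33% at 0.5 and 96% at 0.7. These figures rest on an assumed correlation, 1:1 allocation, 135 evaluable patients per arm and a roughly linear relation between the two sums. The lower end is modest and cannot be ruled out from the documents. The planned 286 patients and the primary analysis are unaffected. The change is worth making because the gain is nearly free and the stated model needs replacing in any case.

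**What to change.** Under Statistical Analysis, take residual ST-segment deviation out of the logistic regression sentence and state a linear model for it. The outcome is the post-procedure sum, or log(sum + 1) if skewed. The terms are:

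- treatment arm;
- the presentation sum of ST deviation, read 60 ms after the J-point over the 12 leads common to both ECGs, on the same scale as the outcome;
- infarct-related artery (LAD vs. non-LAD), which Endpoints Assessment already lists as a subgroup factor.

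Report the adjusted mean difference with its 95% CI. Do not substitute an unadjusted change score, which loses precision at correlations below 0.5. Fix the covariates and the rule for transforming before unblinding, so that the adjustment cannot be chosen on the result.

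The cost is one or two sentences of text and the work of deriving the presentation sum over the common leads from ECGs already taken. No extra recording, visit or patient is needed.
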